### Sample size

A power analysis was conducted and it revealed a sample size of 150 children is sufficient to detect a minimum effect size of 0.12 (Cohen’s ƒ2) with 10 predictors at 80% power and a probability level of 0.05.

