**Methods/Design:**

This study will use a prospective, cross-sectional multi-centre observational design. Children (aged 6–12 years) with unilateral cerebral palsy will be recruited from one of five Australian treatment centres. We will examine associations between cognition, bimanual performance and brain neuropathology (lesion type and severity) in a sample of 131 children. The primary outcomes are: Motor - the Assisting Hand Assessment; Cognitive - Executive Function; and Brain – lesion location on structural MRI. Secondary data collected will include: Motor - Box and Blocks, ABILHAND- Kids, Sword Test; Cognitive – standard neuropsychological measures of intelligence. We will use generalized linear modelling and structural equation modelling techniques to investigate relationships between bimanual performance, executive function and brain lesion location.

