### Primary aim

To examine the association between EF and bimanual performance in children with unilateral CP, whilst accounting for general intellect and unimanual capacity.

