### Study setting and recruitment

Children will be identified from five tertiary paediatric treatment centres across Australia. Children will be recruited from: Monash Children’s Hospital, Victoria; Royal Children’s Hospital, Victoria; Cerebral Palsy Alliance, New South Wales; Lady Cilento Children’s Hospital, Queensland and; Princess Margaret Hospital, Western Australia. The lead investigator, or HREC approved delegate at each trial site will identify potential participants and provide written and verbal information about the study to potential families. Eligibility will be determined through discussion with parents and/or review of medical files. The first child was enrolled in this study on 5th December 2012. Data collection was completed for 131 children on 7th October, 2015.

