### Statistical considerations

Data entry will be undertaken by the Chief Investigators (BH, CI) and research assistants. All statistical analyses will be led by a biostatistician and the Chief Investigators in consultation with the research team. Stata Statistical Software version 15 will be used for analysis. Statistics will be reported with 95% confidence interval, where appropriate, and 5% level of significance will be used.

Data will be analysed using structural equation modelling (SEM). Given the complexity of the model, confirmatory factor analysis (CFA) will be initially conducted on the four elements of EF (cognitive flexibility, goal setting, attention control and information processing) to ensure that three or four chosen measures of each element correlate well and measure the selected element. Regression based-factor scores from the CFA will then be used in the subsequent SEM that incorporates the variables in the model, presented in Fig. 1. The SEM will be used to examine the direct and indirect relationships among between EF (estimated using the BRIEF questionnaire and also the latent variable estimated using the four elements of EF). The model will be adjusted for child characteristics, unimanual capacity and intellectual functioning. For both CFA and SEM, goodness of fit of the final models will be assessed using the chi-square test statistic and goodness of fit indices, particularly the Root Mean Square Error of Approximation (RMSEA), goodness-of-fit index (GFI), Tacker-Lewis index (TLI) and the comparative fit index (CFI). Low levels of missing data are anticipated therefore no missing data imputation is planned and the analyses will explore the appropriateness of using the either maximum likelihood (ml) or maximum likelihood with missing values (mlmv) estimators.

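### The power statement assumes 150 children, but data collection closed at 131 and the power was not restated; the figure also belongs to a whole-model test, not to the adjusted EF association

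*Protocol article*

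**What the plan says.** The Sample size section is one sentence. It states that "a sample size of 150 children is sufficient to detect a minimum effect size of 0.12" (Cohen's f²) "with 10 predictors at 80% power and a probability level of 0.05". It does not say whether f² refers to the whole model or to one predictor, nor how many of the 10 predictors are under test.

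Two other places give a different number. Study setting and recruitment states: "Data collection was completed for 131 children on 7th October, 2015". The Methods/Design part of the abstract describes associations examined "in a sample of 131 children". Nothing links 131 to 150, and the power is not recalculated.

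The Primary aim is: "To examine the association between EF and bimanual performance in children with unilateral CP, whilst accounting for general intellect and unimanual capacity". The primary hypothesis is framed the same way. Under Cognitive outcomes, a single parent-rated score, the overall BRIEF composite, is named as the primary EF measure. Statistical considerations sets the test level ("5% level of significance will be used") and plans a structural equation model (SEM) in which EF enters both through the BRIEF and as a latent variable, adjusted for child characteristics, unimanual capacity and intellectual functioning.

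**The concern.** There are two separate issues.

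- **Sample size.** The number was final when the article was written, yet the only power figure is for 19 more children (150 − 131). A reader will take 80% power at f² = 0.12 as a property of the study as carried out.
- **Test.** The figures fit a test of whether the predictors jointly explain any variation in bimanual performance. Unimanual capacity or IQ alone could make that test significant and leave the EF question open.

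What is at stake is how the EF result is read. Someone who takes 0.12 as the smallest detectable EF effect would misjudge a null finding. Someone who takes it as whole-model sensitivity would credit 131 children with more than they provide.

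**Working it through.** **Inputs.** From Sample size: f² = 0.12, 10 predictors, 80% power, alpha 0.05, N = 150. From Study setting and recruitment: N = 131.

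**Formula.** F test in multiple regression with p = 10 predictors in the model, of which u are tested. Denominator df v = N − p − 1 = N − 11; noncentrality λ = f² × N. Power = P(F′(u, v, λ) > F at the 0.95 quantile on u, v df).

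**Step 1: reproduce the stated figure (overall test, u = 10).**
- N = 150: v = 139, λ = 0.12 × 150 = 18.0, critical F = 1.899, power **81.8%**.
- Smallest N for 80%: 145 (v = 134, λ = 17.4, power 80.1%).

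So 150 is indeed sufficient for this test. With the variant λ = f² × v, power at 150 is 78.1% and 156 are needed, which is also close.

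**Step 2: could it be another test?** All rows have f² = 0.12 and 10 predictors in the model.

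| Predictors tested (u) | N for 80% power | Power at 150 |
|---|---|---|
| 1 | 68 | 98.8% |
| 2 | 84 | 97.2% |
| 3 | 96 | 95.4% |
| 4 | 105 | 93.5% |
| 8 | 134 | 85.7% |
| 9 | 140 | 83.7% |
| 10 | 145 | 81.8% |

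The overall test lies closest to the stated pair of 150 and 80%. A single coefficient is far from it.

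**Step 3: the same overall test at the achieved size.**
- N = 131: v = 120, λ = 0.12 × 131 = 15.72, critical F = 1.911, power **74.5%**. That is 5.5 points below the stated 80% and 7.3 below the 81.8% at 150.
- f² giving 80% power at 131: **0.134**, or R² = 0.1336 / 1.1336 = 0.118. The stated 0.12 corresponds to R² = 0.12 / 1.12 = 0.107.

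**Step 4: one EF coefficient at the achieved size (u = 1, 10 predictors in the model).**
- If partial f² = 0.12: v = 120, λ = 15.72, critical F = 3.920, power **97.6%**.
- Partial f² giving 80% power: **0.061**. Partial R² = 0.0609 / 1.0609 = 0.057, so partial r = √0.057, about 0.24. At 150 children the corresponding f² is 0.053 (partial r about 0.22).

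The article gives no partial effect for EF. Over an assumed range, power at 131 is:

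| Partial f² for EF (assumed) | Power at N = 131 |
|---|---|
| 0.02 | 36% |
| 0.04 | 62% |
| 0.06 | 79% |
| 0.08 | 89% |
| 0.12 | 97.6% |

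**The case against.** The strongest reply is that the sentence contains no arithmetic error. It says what 150 children would deliver, and they do deliver it. That stands: the fault is that the statement was not carried over to 131.

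A reader might put the two issues together and infer that the primary analysis is doubly underpowered. The documents do not support that, because the issues pull in opposite directions. Losing 19 children lowers the power of the overall test, whereas a single coefficient at the same f² needs only 68 children. Nor do the documents show that EF power is ample, since a whole-model f² of 0.12 and a partial f² of 0.12 are different quantities and only an unlabelled value is given.

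It is also fair to say that the overall test is an inference. The section does not name the test, and 150 would suffice for sets of 8 or 9 predictors too. Overall is the most plausible reading, not the only one.

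The planned analysis is an SEM, with EF also modelled as a latent variable. Any single-coefficient regression figure, 0.061 included, is therefore an approximation and must be labelled as one. The protocol's own calculation has the same limit.

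Finally, recruitment is over, and the article already promises 95% confidence intervals where appropriate. These will show the precision of the EF estimate directly. This limits the consequence but does not remove the disagreement between sections.

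**Conclusion.** The concern holds as a reporting fault in the power statement. The article justifies its size at 150, reports 131, and leaves the power as it was. On its own inputs, and reading the calculation as the overall 10-df test, power at f² = 0.12 is 74.5% rather than 80%, or equivalently the detectable f² is 0.134 rather than 0.12. The statement also gives no sensitivity for the adjusted EF association, which is the primary question.

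It is not a finding that the study is too small for its primary aim. With 131 children and 10 predictors, one coefficient is detectable with 80% power at partial f² of about 0.061, roughly half the stated value. Whether the true EF effect is that large cannot be judged from the article.

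These figures assume fixed-predictor regression with 10 predictors, complete data on all 131 children and a two-sided 5% level. The consequence is moderate: no estimate or planned test changes, but the stated benchmark for reading the results does.

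**What to change.** Rewrite the Sample size statement so that it:

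1. says that the calculation assumed 150 children and that data were completed for 131. The article gives no separate number enrolled, so 131 should not be called the number enrolled;
2. names the test, after the authors confirm it. If it is the overall test of 10 predictors, give its value at 131: 74.5% power at f² = 0.12, or 80% power at f² = 0.134;
3. adds the sensitivity for the primary question, for example: *As a multiple-regression approximation to the planned structural equation model, 131 children with 10 predictors give 80% power at a two-sided 5% level to detect a single EF coefficient of partial f² = 0.061 (partial r about 0.24).*

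The cost is two or three sentences. No further enrolment and no change to the analysis are needed. The overall figure becomes somewhat less favourable, and the article gains a figure that addresses the EF question.

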### Study setting and recruitment

Children will be identified from five tertiary paediatric treatment centres across Australia. Children will be recruited from: Monash Children’s Hospital, Victoria; Royal Children’s Hospital, Victoria; Cerebral Palsy Alliance, New South Wales; Lady Cilento Children’s Hospital, Queensland and; Princess Margaret Hospital, Western Australia. The lead investigator, or HREC approved delegate at each trial site will identify potential participants and provide written and verbal information about the study to potential families. Eligibility will be determined through discussion with parents and/or review of medical files. The first child was enrolled in this study on 5th December 2012. Data collection was completed for 131 children on 7th October, 2015.

### Data collection

#### Demographic Data

Basic demographic and clinical information will be collected from families and health records and documented using a using a standardised clinical record form. Information includes: age, diagnosis, gender, gestational age, birth weight, co-morbidities, current schooling and integration assistance, family makeup, medication, seizure history and previous MRI.

#### Clinical Assessment

Children will be assessed within six weeks of recruitment across one or two appointments. A detailed study assessment manual developed by the Chief Investigators (BH, CI) will provided to each site. Clinical assessment will be undertaken by occupational therapists, neuropsychologists or supervised psychologists, all educated in study aims and assessment protocols. Experienced paediatric radiologists will code for lesion characteristics. The radiologist will be blinded to the results of the clinical assessments. The clinical assessors will be blinded to the type of brain lesion.

#### Classification measures

For descriptive purposes, children’s functional level will be classified using the Manual Ability Classification System (MACS) [92], Gross Motor Function Classification System (GMFCS) [93] and Communication Function Classification System (CFCS**)** [94].

#### Upper Limb Motor Performance

##### Primary

**Assisting hand assessment**

The Assisting Hand Assessment (School Kids Version 5.0) will be used to measure bimanual performance (AHA) [95, 96]. The AHA is a standardized, criterion-referenced test for children aged 18 months to 12 years, who have unilateral upper limb impairment. It aims to measure how effectively a child uses their affected hand in bimanual play activities. The AHA will be conducted by video observation of the child using specific toys of the AHA test kit to play one of two board games. The 20 items define different actions and will be scored by a certified AHA rater (occupational therapist) on a 4-point rating scale. The sum of raw scores (sum score) varies between 20 (low ability) to 80 (high ability). Raw scores are converted to interval level data using Rasch analysis. Rescaled logit-based AHA units ranging from 0–100 will be used for data analysis [95]. A higher number indicates higher ability. The psychometric properties of the AHA have been described in several studies [95, 97–99].

##### *Secondary*

**Box and blocks test**

The Blocks and Box Test aims to measure manual dexterity by having a child move as many 2.5 cm blocks as they can from one side of a box, over a low partition to the other side of the box, one-by-one, in one minute [100]. The Box and Blocks Test has age norms for children aged 3 to 10 years [101] and 6 to 19 years [102]. Test-re-test reliability coefficients for adults is reported as r = 0.976 for the right hand, and r = 0.937 for the left hand [100].

ABILHAND-Kids

The ABILHAND-Kids is a questionnaire about manual ability in self-care activities in children with upper limb impairment [103]. The scale consists of 21 mostly bimanual items rated by parents as impossible, difficult, easy to complete or unknown. Scores on the ABILHAND-Kids are significantly related to school education, type of CP, and gross motor function but not age, gender or handedness [104]. Its range and measurement precision are appropriate for clinical practice (reliability: r = 0.94; reproducibility over time: r = 0.91) [103].

Anticipatory action planning

The Sword Test will be used to measure anticipatory action planning [105]. Children will be asked to use their dominant hand to grasp the handle of a plastic sword that has been placed randomly in one of six positions on a template board. Children are required to place the sword into a hole in a wooden block. Some of the sword positions on the template are control positions and others are “critical” positions and require children to plan and make an adjustment to the way they approach and grasp the sword so it is inserted in the hole in a position of end comfort. The dependent variable is whether the posture of the hand at the end of the action is comfortable. For data analyses the proportion of comfortable end postures in the critical conditions and the control conditions will be used. Thus, for every child there are two scores, an average for the critical conditions and an average for the control conditions. Test–retest and inter-rater reliability for the Sword Test is excellent, with an intraclass correlation coefficient (ICC) score of .90 and .95 respectively [106].

#### Cognitive outcomes

##### *Primary*

**Executive function**

We have schematically mapped each of the assessment tasks to Anderson’s [58] four-domain model of child EF, demonstrated in Fig. 1. In this model, the four domains are attention control (which includes selective attention, self-regulation, self-monitoring, and inhibition), information processing (efficiency, fluency, and speed of producing) cognitive flexibility (the ability to divide attention and shift between response sets, complex span/working memory and feedback utilisation), as well as a goal setting component (including efficient idea generation, as well as the ability to initiate and plan goals). In this study, we will also include a broad measure of overall EF that subsumes all of the four subdomains.

**Fig. 1 Fig1:**
[figure not shown]
Proposed model of executive function, bimanual performance and neuropathology with corresponding assessments

As an overall composite measure of EF, the Behaviour Rating Inventory of Executive Function (BRIEF) – Parent Version [68] will be used to obtain parent ratings of current functional, emotional and behavioural manifestations of executive dysfunction. This is an 86-item questionnaire, valid for use in children 5–18 years. T-scores provide information on functioning relative to the standardised sample (mean = 50, standard deviation = 10). Two indexes will be used for analysis. The overall General Executive Composite Score will be the primary measure. A higher score indicates a higher level of executive dysfunction, with a score above 65 indicating abnormal EF. The Metacognition Index and Behavioural Regulation Index will be the secondary outcome. Higher scores indicate greater difficulties with EF.

*(a) Attention contro*

Attention control abilities will be assessed using the Test of Everyday Attention for Children (TEA-Ch) [107]. The TEA-Ch comprises nine subtests, and is valid for children 6–16 years. The scaled scores have a mean = 10 and standard deviation = 3. Attention control will be assessed using the Sky Search task. Children will be given an A3 sheet with rows of space-craft and asked to find all targets (an identical pair of space craft). Children mark a box when they are finished. Total number of correct targets and time taken will be recorded.

*Self-monitoring, self-regulation and inhibition* will be measured using the Inhibition task of the NEPSY-II, designed for children 5–16 years. Children are screened for basic naming of included shapes, and then are asked to look at a series of black and white shapes or arrows and name either the shape, direction, or an alternative response, depending on the colour of the shape or arrow. Inhibition of automatic responses to stimuli is required for successful task completion. Scaled scores are calculated (mean = 10, standard score = 3) using age-based normative data for each of the described areas.

*(b) Cognitive flexibility*

*Divided attention* will be measured using the Sky Search DT task from the TEA-Ch. This requires a test score from the SCORE task also. In the Score! Task, children are first asked to count to 10 as a screen. Then, children continuously count tones for 10 items (in which tones are separated by silent inter-stimulus intervals of variable duration between 500 and 5000 msec). Counting to 15 will be tested as a pre-requisite for this task. In Sky Search DT, children are required to complete the Score! and the Sky Search tasks simultaneously. Decrements in task performance relative to performances on isolated tasks will be computed as a measure of attention decrement under dual-task conditions.

*Working memory* will be assessed using tasks from the Automated Working Memory Assessment Visuospatial (AWMA) [66]. The AWMA is a computer administered test valid for use in children and adults (4–22 years). Children will complete two tasks tapping visuospatial short term (Dot Matrix, Block Recall) and two visuospatial working memory tasks (Mr X, Backwards Dot Matrix).

*Feedback utilisation* will be measured using the Inhibition Switching Task and scores from the NEPSY II. This task builds on the Inhibition naming task, and includes an attentional switching component, providing naming accuracy and speed scores.

*(c) Speed of information processing*

*Efficiency* and *fluency* will be calculated using specific test scores from the Word generation/fluency subtest from the NEPSY-II [108] as well as the Tower of London (TOL) task [109]. The NEPSY-II word generation/fluency task is designed for use in children 3–16 years, and provides age based scaled scores (mean = 10, SD = 3). Children will be required to rapidly name words based on semantic and phonemic (initial letter) cues.

The TOL task involves children completing 12 ‘problems’ in which they are required to rearrange three coloured balls on posts so that a new configuration corresponds to the pattern presented on a stimulus card. Normative data from Anderson et al. [110], will be used to transform raw scores into age based standard scores (mean = 100, SD = 15). Efficiency will be calculated using the TOL move accuracy ratio.

Fluency will be calculated using the total number of words generated in the NEPSY-II word generation task (including errors).

Basic *speed of processing* will be measured using the processing speed index, calculated from the WISC-IV. In order to provide a measure of processing speed independent of fine motor function, the Speeded Naming task from the Neuropsychology Assessment for Children-II (NEPSY-II) [108] will also be used.

*(d) Goal setting*

Goal setting includes a number of sub components. Initiative is the ability to develop new concepts, measured by the total number of correct words in the word generation/fluency subtest from the NEPSY-II [108]. The total time required to plan the first move on the TOL provides a measure of planning, using additional process scores calculated according to guidelines provided by Anderson et al. [110]. The TOL total correct provides a measure of strategic organisation. The Rey Complex Figure Test (RCFT) assesses a child’s ability to strategically organise their response to a complex problem. Strategic organisation scores will be calculated as per Anderson et al. [111].

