### Executive function

Executive functions (EFs), often referred to as higher-level cognitive functions [55], are defined as those “metacognitive capacities that allow an individual to perceive stimuli from his/her environment, respond adaptively, flexibly change direction, anticipate future goals, consider consequences, and respond in an integrated or common-sense way, utilising all these capacities to serve a common purposive goal” [56]. In line with Alexander and Stuss [57] and Anderson [58], EF has been conceptualised with four distinct domains: (i) attentional control, (ii) information processing, (iii) cognitive flexibility, and (iv) goal setting. EFs are dependent on numerous and complex neuronal systems within the prefrontal cortex and with virtually all other brain regions including the brain stem, occipital, temporal, and parietal lobes, as well as the limbic and subcortical regions [59]. It is the last cognitive function to mature [60] and evolves over a prolonged period of time through brain maturation and life experiences in childhood and adolescence. Each of the four domains of EF has a separate developmental trajectory, yet EF processes operate in an integrative manner.

There are a growing number of studies [22, 33, 43, 53, 61–65] and reviews [38, 66, 67] that have investigated EF in children with CP with findings suggesting difficulties across multiple EF domains. Bottcher et al. [43] report difficulties in all domains of the Behavior Rating Inventory of Executive Function (BRIEF) [68] in a group of 33 children with spastic unilateral and bilateral CP. Bodimeade et al. [53] found children with unilateral CP performed significantly more poorly than typically developing peers on most EF measures, irrespective of side of hemiplegia. Contrary to these findings, Stadskleiv et al. [64] investigated EF in in a population of children with spastic CP and speech/motor impairment. They used a novel test battery comprised of alternative assessment measures and some experimental questionnaires to measure EF and found performances were in the normal range. Further, they investigated the factor structure of the four-domain model of EF described by Anderson et al. [58] and these findings did not support the model of EF proposed by Anderson et al. [58]. However, the validity of these novel measures is unclear.

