### Participants

#### Inclusion Criteria

Children will be eligible to participate if they have a confirmed diagnosis of unilateral CP as reported in the medical history by a medical specialist (i.e. neurologist, paediatrician), are aged 6 to 12 years at the time of assessment, present to one of five participating sites (between July 2012 and August 2015), and have sufficient cooperation and language skills to complete the assessments.

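### Two word-count indicators have no stated age conversion yet enter the executive function CFA beside age-standardised scores, so the latent EF and sub-domain scores may carry age as well as impairment

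*Protocol article*

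**What the plan says.** All references are to the protocol article.

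- **Age range.** Under Inclusion Criteria, children "are aged 6 to 12 years at the time of assessment". The Background section on executive function says that EF "evolves over a prolonged period of time through brain maturation and life experiences in childhood and adolescence" and that "Each of the four domains of EF has a separate developmental trajectory".
- **Indicators worded as counts.** Under (c) Speed of information processing: "Fluency will be calculated using the total number of words generated in the NEPSY-II word generation task (including errors". Under (d) Goal setting, initiative is the number of correct words on the same subtest. No age conversion is attached to either definition.
- **Indicators that are age-standardised.** NEPSY-II Inhibition is given as scaled scores from age norms. For the Tower of London (TOL), normative data "will be used to transform raw scores into age based standard scores". The WISC-IV processing speed index is a standard score.
- **Indicators whose form is unclear.** For planning, "The total time required to plan the first move on the TOL provides a measure of planning". For Sky Search, "Total number of correct targets and time taken will be recorded", although scaled scores are cited for the TEA-Ch battery.
- **Analysis.** Under Statistical considerations, the CFA comes first, "to ensure that three or four chosen measures of each element correlate well and measure the selected element". Regression-based factor scores then go into the SEM. The SEM is adjusted for child characteristics, unimanual capacity and intellectual functioning. Age is collected as demographic data but is not named as an adjuster, and no age adjustment is stated for the CFA.

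**The concern.** Where EF matures with age, a raw count of words rises with age in impaired and unimpaired children alike, so an impaired 12-year-old can outscore a typical 6-year-old. An age-normed score has that trend removed. Putting both kinds into one factor has three consequences.

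- The CFA check on whether measures of a domain belong together is partly a check on which of them share age. Raw indicators gain correlation through age, and raw-with-scaled pairs lose some.
- The factor scores inherit age, to a different degree in each domain, so sub-domain associations with bimanual performance are not on an equal footing. Fluency and initiative come from the same subtest and sit in two different domains, so any shared age trend blurs that contrast further.
- Assisting Hand Assessment units are logit-based and are not described as age-normed. If they also rise with age, an age-laden EF score would be associated with them through age alone. Adjusting for WISC-IV intelligence would not remove this, because those scores are already age-normed.

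At stake are the secondary aim on EF sub-domains and the latent EF variable that the SEM uses alongside the BRIEF.

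**Working it through.** The documents give no figure for how strongly these scores track age. The only design calculation (150 children, f² = 0.12, 10 predictors, 80% power) does not enter this point. It reproduces acceptably: the overall F test with noncentrality f²·N gives 81.8% power at 150.

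**Inputs from the document:** ages 6 to 12, and three or four indicators per domain.

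**Assumptions:** correlation a = 0.4 to 0.7 between a raw indicator and age; correlation w = 0.3 between any two indicators at a given age; zero correlation of an age-normed indicator with age; three indicators with equal weights.

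**Step 1. Correlations between indicators.**
- Scaled with scaled: w = 0.30.
- Raw with scaled: s = w·√(1 − a²). For a = 0.4, 0.3 × 0.917 = 0.275. For a = 0.7, 0.3 × 0.714 = 0.214.
- Raw with raw: m = a² + (1 − a²)·w. For a = 0.4, 0.16 + 0.84 × 0.3 = 0.412. For a = 0.7, 0.49 + 0.51 × 0.3 = 0.643.

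**Step 2. Share of composite variance explained by age.** With k raw indicators the share is (k·a)² divided by the variance of the sum.

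| Raw indicators of 3 | Variance of the sum | a = 0.4 | a = 0.7 |
|---|---|---|---|
| 1 | 3 + 2(w + 2s) | 0.16 / 4.700 = 3.4% | 0.49 / 4.457 = 11.0% |
| 2 | 3 + 2(m + 2s) | 0.64 / 4.924 = 13.0% | 1.96 / 5.143 = 38.1% |
| 3 | 3 + 6m | 1.44 / 5.472 = 26.3% | 4.41 / 6.858 = 64.3% |

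**Step 3. Which row applies.** Information processing contains one indicator worded as raw (fluency) beside TOL efficiency, the WISC-IV index and Speeded Naming, so row 1 is the reading the text supports. Goal setting has one (initiative), or two if TOL planning time is outside the age conversion, which gives row 2. The text shows no domain in row 3.

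**Step 4. Check with factor scores instead of equal weights.** Assume a one-factor model with three indicators, within-age loadings of 0.6, ages uniform from 6 to just under 13 (SD 7/√12 = 2.02 years), and a raw-score slope of 0.1 to 0.4 within-age SD per year.
- All indicators scaled: the score is uncorrelated with age, and its correlation with age-relative EF is √(1.6875/2.6875) = 0.79, where 1.6875 = 3 × 0.36/0.64.
- One raw indicator: age explains 0.7% to 4% of the score.
- Two raw indicators: age explains 3% to 45%, and the correlation with age-relative EF falls from 0.78 to 0.56 across the slope range. At the steepest slope the loadings become 0.36 for the scaled indicator and 0.78 for each raw one.

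**Step 5. What an age term in the SEM would recover.** In the worst case of step 4 the factor-score weights, on the within-age scale, are 0.095, 0.365 and 0.365 (sum 0.825, sum of squares 0.275). With age held fixed, the correlation with EF is 0.6 × 0.825 / √(0.64 × 0.275 + 0.36 × 0.825²) = 0.495/0.649 = 0.76, close to 0.79. A linear age term in the SEM thus repairs most of the score's validity, but not the CFA loadings or fit on which the domain check rests.

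**The case against.** The strongest reply is that most indicators are not shown to be raw. The TOL conversion may well cover planning time, since the process scores come from the same cited source. Sky Search targets and time are only said to be recorded, and TEA-Ch scaled scores are cited. The word-generation subtest is said to provide age-based scaled scores, so initiative could enter in that form. The article also refers to a detailed assessment manual, and its indicator map (Fig. 1) is not shown. If age is among the child characteristics, step 5 shows that the SEM paths are largely protected.

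Much of this stands. A reader might infer that raw and scaled scores are mixed throughout the four domains, that the domains measure age instead of impairment, or that a quarter to two thirds of a domain score is age. The document does not support any of these: the 26% to 64% range needs three raw indicators in one domain. A reader might also expect raw and scaled indicators to fail to correlate. On the model above the correlation only falls from 0.30 to between 0.21 and 0.27.

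The reply does not dispose of the fluency score. Its definition is explicit, it includes errors, and no norm is stated for such a total. Where the authors intend conversion for Inhibition and the TOL, they say so. Nor is this only a detail left to another document: the article defines the score and the order of analysis, and that order forms the factor scores without an age adjustment.

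**Conclusion.** The point holds in limited form. Fluency, and initiative as worded, are counts with no stated age conversion in a CFA that also contains age-standardised scores, and no age adjustment is stated before factor scores are formed. The latent EF variable and the sub-domain scores may carry age as well as impairment. With one raw indicator in a domain the effect is small: about 3% to 11% of an equally weighted composite, or 0.7% to 4% of a factor score under the second set of assumptions. With two, which is possible only in goal setting, it is material: 13% to 38%, or 3% to 45%. All these sizes rest on assumed age correlations, slopes and loadings. The BRIEF General Executive Composite is a T-score and is unaffected, so the primary EF measure stands. The change is worth making because it is almost free and protects the secondary aim.

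**What to change.** 1. State the score form of every CFA indicator and make each one age-standardised. Use the published scaled or standard scores the article cites wherever they apply (TEA-Ch, NEPSY-II, TOL).
2. For an indicator without a stated norm, such as words including errors, use the residual from a within-sample regression on age, or put age in the CFA as a covariate.
3. Say whether the TOL age conversion covers time to first move.
4. Name exact age among the child characteristics in the SEM. It is needed in any case for the Assisting Hand Assessment, which is not described as age-normed.

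The cost is a scoring rule and a rerun on data already collected from 131 children. The one downside is that sample-based residuals, for the few indicators without norms, remove the average age trend of this sample and do not place a child relative to typically developing peers.
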